#### Quality improvement-related indicators

The rate of first-time pulmonary surfactant administration via MISA among all preterm infants with a gestational age of 23–29 + 6 weeks admitted to the NICU and the trend of this rate changing over years.The success rate of MISA (defined as the completion of pulmonary surfactant administration under non-invasive support, without early termination of administration or switching to tracheal intubation for administration).The rate of DCC among all preterm infants with a gestational age of 23–29 + 6 weeks admitted to the NICU and the trend of this rate changing over years.

### Data collection and diagnoses

Demographic data will include gestational age, birth weight, sex, multiple births, antenatal corticosteroid use, mode of delivery, maternal complications, Apgar score, and cord blood gas levels. Clinical data will encompass survival rates, required doses and timing of surfactant administration, blood gas measurements on the first day after birth, need for mechanical ventilation during hospitalization, duration of NCPAP/NIPPV, days on supplemental oxygen, hospitalization costs, and morbidity of BPD, pneumothorax, nasal trauma, pulmonary hemorrhage, hsPDA, IVH, PVL, blood culture-confirmed late onset sepsis, NEC, and ROP.

Pneumothorax will be diagnosed by the presence of air in the pleural cavity in a chest x-ray. Pulmonary hemorrhage will be diagnosed based on the gushing of bloody fluid from the upper airway or endotracheal intubation and when the chest x-ray is consistent with the relevant clinical findings. The diagnosis for hsPDA will be based on clinical signs and echocardiogram. IVH and white matter injury will be diagnosed by cranial ultrasound examination, and IVH will be graded by the Papile classification system. Blood culture-confirmed sepsis will be defined as clinical sepsis with evidence of pathogens in blood culture. NEC will be graded according to the modified Bell's classification system. The diagnosis and staging of ROP will be based on retinal examination by a consultant ophthalmologist.

Pneumothorax will be diagnosed radiographically by detecting air within the pleural cavity on chest radiography. Pulmonary hemorrhage is defined as acute onset of frank blood emanating from the upper airway or endotracheal tube, accompanied by radiographic evidence concordant with clinical manifestations. The diagnosis of hsPDA will be established through integration of clinical indicators and confirmatory echocardiography (13). IVH and PVL will be identified via standardized cranial ultrasonography, with IVH severity classified according to the Papile grading system (14). Culture-confirmed late-onset sepsis requires both compatible clinical signs and isolation of pathogenic microorganisms from blood cultures. NEC will be staged using the modified Bell's classification criteria (15). ROP diagnosis and staging will be determined through comprehensive retinal evaluations performed by a certified ophthalmologist.

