#### Inclusion criteria

① Infants of 23–29 + 6 weeks gestational age.② Born in Peking University Third Hospital, having spontaneous breathing after birth;③ Diagnosed as NRDS; NRDS is defined as progressive dyspnea that occurs after birth, with or without imaging evidence, excluding other causes of dyspnea.

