#### Exclusion criteria

① Premature infants who have received tracheal intubation prior to the use of PS due to resuscitation or other reasons shortly after birth;② Premature infants with identified or confirmed congenital abnormalities (such as fetal edema, chylothorax, or neuromuscular disease) or severe birth complications (including hemorrhagic shock, air leakage, or early-onset sepsis) that impact respiratory function;③ Newborns who discontinue treatment or have incomplete information;④ Newborns involved in other intervention research studies.

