### Statistical analysis

Statistical analyses were conducted using SPSS 20.0 software. Normally distributed data are presented as mean ± standard deviation, with intergroup comparisons performed using one-way analysis of variance (ANOVA) and *post hoc* tests conducted via the Student-Newman-Keuls (SNK) method for Type I error correction. Non-normally distributed data are expressed as median (Q1, Q3), and intergroup comparisons are made using the Kruskal–Wallis test.

For categorical data, counts and percentages are used for intergroup comparisons, employing the *χ*² test with continuity correction or Fisher's exact test as appropriate. The analysis of factors influencing binary outcomes will be performed using binary logistic regression, accounting for potential confounding variables. A *p*-value of <0.05 will be considered statistically significant.

To assess the robustness of the main conclusions of the study, we will conduct the following sensitivity analyses: To control for potential confounding factors as comprehensively as possible, we will include all baseline variables with intergroup differences reaching a significance level of *P* < 0.1 in the univariate analysis, together with the study grouping variable, into the multivariable Logistic regression model. This is to calculate the adjusted odds ratio (aOR) of the effect of DCC + MISA on BPD and its 95% confidence interval (95% CI).

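### Twins and triplets are eligible, but the logistic regression behind the adjusted odds ratio treats every infant as independent, so its confidence interval is somewhat too narrow

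*Protocol article*

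**What the plan says.** Eligibility is defined for the individual infant. The gestational-age criterion reads "Infants of 23–29 + 6 weeks gestational age". None of the four exclusion criteria concerns multiple birth; the last of them is "Newborns involved in other intervention research studies". Under Data collection and diagnoses, multiplicity is a planned baseline item: "Demographic data will include gestational age, birth weight, sex, multiple births".

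Under Research grouping, the three groups are set by calendar period and by the cord and surfactant treatment received.

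Under Statistical analysis, categorical outcomes are compared by the chi-square "test with continuity correction or Fisher's exact test as appropriate". Modelling of binary outcomes "will be performed using binary logistic regression, accounting for potential confounding variables". For the adjusted odds ratio of DCC + MISA on BPD, "we will include all baseline variables with intergroup differences reaching a significance level of" P < 0.1, together with the grouping variable. No random effect, GEE, robust variance or one-infant-per-mother rule is named, and the sample size calculation contains no design effect.

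**The concern.** Siblings from one pregnancy share the mother, her antenatal steroids and complications, and very nearly the gestational age and delivery. Their BPD outcomes are therefore likely to be positively correlated. They also cannot normally fall in different periods. A sibling who misses the treatment criteria of the period drops out instead of joining another group. The clustering is thus within group, which is the case where ignoring positive correlation understates the variance of a between-group contrast.

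Multiple birth can enter the model only as a fixed covariate, and only if it passes the P < 0.1 screen. That removes a mean difference between multiples and singletons. It leaves the correlation between siblings, and so the standard errors, uncorrected.

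The adjusted odds ratio is the article's confounder-adjusted estimate for a non-randomised comparison across eras, so the validity of its interval matters.

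**Working it through.** **The plan's own figure.** Inputs from Sample size calculation: p1 = 0.29, p2 = 0.14, k = 3, z-values 1.96 and 0.84.

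n2 = (1.96 + 0.84)² × [0.29 × 0.71/3 + 0.14 × 0.86] / 0.15² = 7.84 × 0.18903 / 0.0225 = 65.87

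This gives 66 and 3 × 66 = 198, as stated. Then 66/0.9 rounds up to 74, and 3 × 74 = 222. Power at 66/198 is 80.0% if infants are independent, so there is no margin.

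**Clustering.** Two quantities are needed and the article gives neither, so both are assumed:
- f, the share of infants with a sibling enrolled in the same group: 0.2–0.4
- rho, the within-pair correlation of BPD: 0.2–0.5

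For pairs:
- Design effect: DE = 1 + f × rho
- True standard error / naive standard error = √DE
- Interval too narrow by 1 − 1/√DE
- Actual error of a nominal 5% uncorrected test = 2 × P(Z > 1.96/√DE)
- Power at 66/198 of an analysis that uses the correct standard error = Φ(0.15/(√DE × SE) − 1.96), where SE² = 0.29 × 0.71/198 + 0.14 × 0.86/66

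| f | rho | DE | √DE | Interval too narrow by | Error, uncorrected test | Power at 66/198 |
|---|---|---|---|---|---|---|
| 0.2 | 0.2 | 1.04 | 1.020 | 2% | 5.5% | 78.5% |
| 0.3 | 0.3 | 1.09 | 1.044 | 4% | 6.0% | 77% |
| 0.4 | 0.3 | 1.12 | 1.058 | 5% | 6.4% | 75% |
| 0.4 | 0.5 | 1.20 | 1.095 | 9% | 7.4% | 72.5% |

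**Simulation of the named tests.** With 198 against 66 infants, BPD at 29% in both groups and 400,000 runs:
- Uncorrected chi-square: 5.1% with no siblings, 6.0% at f 0.3 / rho 0.3, 6.4% at f 0.4 / rho 0.3.
- Continuity-corrected chi-square: 3.5% with no siblings, 3.9% at 0.2/0.2, 4.2% at 0.3/0.3, 4.6% at 0.4/0.3, 5.3% at 0.4/0.5.
- Continuity-corrected chi-square at 222 against 74: 4.0%, 4.4% and 5.5% at 0.2/0.2, 0.3/0.3 and 0.4/0.5.

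A separate simulation of an unadjusted logistic Wald test over the same range gave 5.2–7.3%, close to the formula.

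**The case against.** A reader might infer that the main comparison as a whole has an error rate above 5%. The documents do not support that. For two-group tables the article names the continuity-corrected chi-square or Fisher's exact test, and both are conservative. The corrected test passes 5% only in the worst corner of the assumed range. This stands, and it confines the inflation to the logistic model and to uncorrected tests. The usual continuity correction applies to 2 × 2 tables, so it would not protect an overall three-group test, and it does nothing for the adjusted odds ratio.

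The size can also be disputed, on two grounds that both stand:
- The interval of the adjusted odds ratio depends on residual correlation. Gestational age, steroids and delivery mode are recorded. Where they enter the model, they absorb part of what siblings share. Era is largely the grouping variable and adds little correlation within a group.
- Each sibling must separately meet the breathing, respiratory distress, no-prior-intubation, cord-timing and surfactant rules. A multiple birth with only one qualifying infant contributes no pair, which lowers f.

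Finally, the article never says in words that infants are independent, and a condensed article may leave the variance estimator to a fuller document. This stands only in part. The methods are named, and as named they assume independence, so following the text as written gives standard errors that are too small. A reader should not go further and infer that the investigators have ruled out a clustered analysis.

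**Conclusion.** The point holds for the adjusted odds ratio, its confidence interval and tests without continuity correction. Under the assumed 20–40% of infants with an enrolled sibling and a correlation of 0.2–0.5, intervals are about 2–9% too narrow and the nominal 5% level is really about 5–7%. The lower part is more likely once gestational age and steroids are in the model.

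The direction rests on siblings being positively correlated and mostly in the same group, which the calendar-based grouping makes likely. The size cannot be fixed from the article. It is modest, and secondary to the bias between eras that the article's limitations already acknowledge. It is still worth correcting, because a better method is available at little cost and prospective collection is planned to run to October 2027.

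**What to change.** Record a maternal identifier for every infant in all three groups. Fit the logistic models for BPD, survival and the other binary outcomes by GEE, with mother as the cluster and an exchangeable working correlation, or use cluster-robust standard errors by mother. Take the adjusted odds ratio, its 95% interval and its p-value from that model. Multiple birth may stay as a covariate, but not as a substitute for clustering.

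The cost is one sentence in Statistical analysis and one extra variable in the dataset. GEE is available in SPSS, the stated software. Intervals become slightly wider. If few sibling pairs are enrolled, the results will barely change.

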### Safety procedures

This study is observational in nature. Should any adverse events occur, they will be accurately documented, and appropriate medical treatment will be provided.

### Sample size calculation

Our hospital has previously conducted a prospective multicenter clinical study comparing MISA and tracheal intubation in the early stages. The results indicated that the incidence of BPD in premature infants with a gestational age of less than 30 weeks was 29% in the MISA group (*n* = 31) and 70% in the tracheal intubation group (*n* = 20). Assuming the BPD incidence rate (p_1_) in the ICC + MISA group for this study is 29%, and the incidence in the DCC + MISA group (p_2_) decreases by 15%–14%, we will set the Type I error (α) at 0.05 and the Type II error (β) at 0.2. With a sample size ratio (k) of 3:1 between the DCC + MISA and ICC + MISA groups, the sample size calculation formula is:$$n_{2}=\frac{{\left(z_{1-a/2}+z_{1-\beta }\right)}^{2}[\;p_{1}(1-p_{1})/k+p_{2}(1-p_{2})]}{{\left(\;p_{1}-p_{2}\right)}^{2}}$$*n*_1_ = *k* × *n*_2_.

Where z_(1−*α*/2)_ = 1.96 and _z(1−*β*)_ = 0.84.

This results in a sample size of 66 for the DCC + MISA group and 198 for the ICC + MISA group. Assuming a 10% loss to follow-up, the adjusted sample sizes will be 74 for the DCC + MISA group and 222 for the ICC + MISA group. Additionally, the sample size for the ICC + tracheal intubation group is also set at 222 cases.

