#### ICC+MISA group

From Jan.1, 2021 to Dec. 31, 2024.Umbilical cord clamping is performed within 20 s after birth. Infants are diagnosed with NRDS and receive a therapeutic dose of PS via MISA within the first 2 h after birth.

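### The stated 80% power rests on a BPD rate from 31 infants in another study, although the ICC + MISA cohort's own rate can be counted now

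*Protocol article*

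**What the plan says.** The Sample size calculation section of the protocol article takes its control rate from an earlier study: "Our hospital has previously conducted a prospective multicenter clinical study comparing MISA and tracheal intubation in the early stages". There, BPD incidence in infants under 30 weeks "was 29% in the MISA group (*n* = 31"). The section carries that rate over, assuming that BPD incidence "in the ICC + MISA group for this study is 29" per cent. For the new regimen, "the incidence in the DCC + MISA group (p_2_) decreases by 15%–14"%, which I read as a fall of 15 percentage points to 14%. On errors: "we will set the Type I error (α) at 0.05 and the Type II error (β) at 0.2". The result is 66 and 198 infants, raised to 74 and 222 for 10% loss.

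The ICC+MISA group section dates that group "From Jan.1, 2021 to Dec. 31, 2024", and the Figure 1 caption also ends the retrospective cohort on 31 December 2024. The Abstract and the Study design section give 2021 to 2025 for the same group. All of these describe its data as retrospective. The prospective DCC + MISA group starts on 31 August 2025. The article reports no BPD rate from the ICC + MISA records and does not show how power changes with the control rate.

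**The concern.** External pilot data are the usual source of a control rate when that rate cannot yet be observed. Here it can be, because the comparator is a historical cohort from the same unit whose records must be abstracted anyway. An infant born at 23 weeks on 31 December 2024 reaches 36 weeks 13 weeks later, on about 1 April 2025, five months before prospective enrolment opens. If the period runs into 2025, most outcomes would still be on file. The planned 222 infants are about seven times the 31 used (222/31 = 7.2). They come from the study's own centre and would be classified under its own BPD definition, whereas the sample size section does not say which definition produced the 29%.

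At stake is how a result from 74 prospective infants is read. If the real power for the stated difference is well below 80%, a non-significant comparison could be taken as evidence that adding DCC brings no benefit.

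**Working it through.** **Inputs** (Sample size calculation section unless noted): p1 = 0.29, p2 = 0.14, z values 1.96 and 0.84, k = 3 with n1 (ICC + MISA) = 3 × n2 (DCC + MISA), loss 10%. The sentence on the ratio, "With a sample size ratio (k) of 3:1 between the DCC + MISA and ICC + MISA groups", names the groups in the opposite order, but the formula and the results make ICC + MISA the larger group.

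**1. The protocol's own figures.**

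n2 = (1.96 + 0.84)² × [0.29 × 0.71/3 + 0.14 × 0.86] / 0.15² = 7.84 × (0.0686 + 0.1204) / 0.0225 = 65.87, so 66, and n1 = 198.

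With loss: 66/0.9 = 73.3, so 74, and 3 × 74 = 222. All four figures reproduce.

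**2. Precision of the 29%.** 29% of 31 is 9 infants (9/31 = 29.0%). The exact (Clopper-Pearson) 95% interval is 14.2% to 48.0%; Wilson gives 16% to 47%.

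**3. Power over that range, protocol's formula.** The documents do not give the 2021–2024 rate, so p1 is varied as an assumption. With SE = √[p1(1−p1)/198 + p2(1−p2)/66], power = Φ(|p1 − p2|/SE − 1.96).

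- 29% v 14%: SE = √(0.001040 + 0.001824) = 0.0535; 0.15/0.0535 − 1.96 = 0.84; power 80%.
- 40% v 25%: SE = √(0.001212 + 0.002841) = 0.0637; 0.15/0.0637 − 1.96 = 0.40; power 65%.

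| p1 | Power, 15-point fall | n2 for 80% power, 15-point fall | Power, same relative fall (p2 = p1 × 14/29) |
|---|---|---|---|
| 14% | not possible | – | 45% |
| 20% | 97% | 36 | 61% |
| 29% | 80% | 66 | 80% |
| 40% | 65% | 94 | 93% |
| 48% | 60% | 107 | 98% |

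The two power columns move in opposite directions.

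**4. A separate effect: the test.** The formula in step 1 uses unpooled variances. The Statistical analysis section names the chi-square test with continuity correction, or Fisher's exact test. Enumerating all outcomes of two independent binomials at the protocol's own rates (29% v 14%), two-sided 5%:

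| Evaluable infants | Unpooled formula | Chi-square, uncorrected | Chi-square, continuity-corrected |
|---|---|---|---|
| 198 v 66 | 80.0% | 71.6% | 65.2% |
| 222 v 74 (no losses) | 84.3% | 76.6% | 71.5% |

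This gap is present with p1 fixed at 29%, so it does not come from the source of p1. The spread over p1 remains under either test: for a 15-point fall at 198 v 66, uncorrected power is 90%, 72%, 61% and 57% at p1 = 20%, 29%, 40% and 48%, and corrected power is 84%, 65%, 54% and 51%.

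**The case against.** The strongest defence is that nothing here is an arithmetic error. The section discloses the source, its size, the formula and the error rates, and its numbers reproduce. Taking a rate from the hospital's own earlier prospective study, in the same gestational-age range and with the same surfactant method, is ordinary practice. The target difference, 29% to 14%, is stated, and the planned adjusted odds ratio with its 95% confidence interval will show what a non-significant result excludes. All of this stands, and it keeps the point minor. It does not explain why an imprecise external figure should be used where a larger internal one can be counted.

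Three stronger readings are tempting, and the documents support none of them:

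- A reader might infer that the 29% is a guess, or that the detectable difference is undisclosed. It is a disclosed but imprecise estimate, and the target is written down.
- A reader might infer that the choice of p1 leaves the study underpowered. The direction is unknown: a higher control rate lowers power for a 15-point fall and raises it for a constant relative fall.
- A reader might attribute the drop from 80% to 72% at 29% versus 14% to the 31 infants. That drop comes from the test.

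It is also fair to object that counting the control rate settles only p1. The 14% target would remain an assumption, so the restated power would still be conditional.

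**Conclusion.** The point holds as a minor, nearly free improvement to a stated figure. Over the exact 95% interval for 9/31, the power that the protocol puts at 80% runs, by its own formula at 198 versus 66, from 97% at p1 = 20% down to 60% at 48% for a 15-point fall. For a constant relative fall it runs from 45% at p1 = 14% up to 98% at 48%. Independently of p1, the 80% overstates what the chi-square test delivers at the protocol's own rates: about 72% uncorrected and 65% with continuity correction at 198 versus 66. The power statement therefore needs restating in any case.

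These results assume that 29% is 9 of 31, that the fall is 15 percentage points to 14%, and that the two groups are compared without covariate adjustment. That the ICC + MISA rate can be counted now is inferred from the dates, since the article does not report it.

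**What to change.** 1. Reconcile the end of the ICC + MISA period: 2024 in its group definition and the Figure 1 caption, 2025 in the Abstract and Study design.
2. Tabulate BPD in that cohort under this study's eligibility criteria and BPD definition, and use the result as p1 in place of 29%.
3. Restate power and the smallest detectable difference for the test that will actually be used, at 198 versus 66 and at 222 versus 74, over a short range of p2. Say plainly that p2 remains an assumption.
4. Leave the enrolment target unchanged, and use no DCC + MISA outcomes in this step.

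The cost is one tabulation of data that must be collected anyway and a revised paragraph. The drawback is that the stated power may become less favourable.

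### The sample size is stated for 80% power, but at 66 versus 198 the planned χ² test has about 65% power with continuity correction and 72% without it

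*Protocol article*

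**What the plan says.** The section Sample size calculation fixes the error rates: "we will set the Type I error (α) at 0.05 and the Type II error (β) at 0.2". The quantiles are 1.96 (two-sided) and 0.84. BPD incidence is taken as 29% with ICC + MISA. The DCC + MISA rate is printed as one that "decreases by 15%–14"%, which reproduces the counts only if read as a fall of 15 percentage points to 14%. The allocation is described thus: "With a sample size ratio (k) of 3:1 between the DCC + MISA and ICC + MISA groups". An unpooled-variance formula for two proportions follows, with n1 = k × n2, and then the result: "This results in a sample size of 66 for the DCC + MISA group and 198 for the ICC + MISA group". The allowance for losses comes next: "Assuming a 10% loss to follow-up, the adjusted sample sizes will be 74 for the DCC + MISA group and 222 for the ICC + MISA group".

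The section Statistical analysis names the test for categorical data as the χ² "test with continuity correction or" Fisher's exact test, as appropriate, judged at p < 0.05. The multivariable logistic model for the effect of DCC + MISA on BPD is listed there as a sensitivity analysis.

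**The concern.** A sample size formula delivers its stated power only for a test with the same standard error. The printed formula has the unpooled variance in both the critical value and the power term. The Pearson χ² uses the pooled variance under the null, and the continuity correction and Fisher's test are stricter still. In equal groups the pooled and unpooled versions nearly agree. Here they do not: the large group has the higher rate, so it dominates the pooled rate, and that inflates the null variance assigned to the small group.

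DCC + MISA against ICC + MISA on BPD is the only comparison the study is sized for. If its power is overstated, a non-significant result will be read as evidence against DCC + MISA from an 80%-powered study, when the chance of missing the assumed effect was well above 20%.

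The ratio sentence adds a contradiction: 66 DCC + MISA and 198 ICC + MISA are 1:3 in the order in which that sentence names the groups.

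**Working it through.** **Inputs** (Sample size calculation): p1 = 0.29 (ICC + MISA), p2 = 0.14 (DCC + MISA), k = 3, z values 1.96 and 0.84, 10% loss. The test comes from Statistical analysis.

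**1. Reproducing the plan's figures**

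- n2 = (1.96 + 0.84)² × [0.29 × 0.71/3 + 0.14 × 0.86] / 0.15² = 65.87, rounded up to 66
- n1 = 3 × 66 = 198
- 66/0.9 = 73.3, rounded up to 74; 3 × 74 = 222

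All four counts reproduce.

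**2. The two standard errors at 66 versus 198**

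- Pooled rate: (198 × 0.29 + 66 × 0.14)/264 = 0.2525
- Null (pooled): √[0.2525 × 0.7475 × (1/198 + 1/66)] = 0.0617
- Unpooled: √[0.29 × 0.71/198 + 0.14 × 0.86/66] = 0.0535

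**3. Power by normal approximation**

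- Plan's formula: Φ(0.15/0.0535 − 1.96) = 80.0%
- Pearson χ²: Φ[(0.15 − 1.96 × 0.0617)/0.0535] = 70.6%
- With continuity correction: subtract ½(1/198 + 1/66) = 0.0101 from the difference. Φ[(0.15 − 0.0101 − 1.96 × 0.0617)/0.0535] = 63.8%

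**4. Exact power**, summing both binomial distributions over every table that the test rejects, two-sided 0.05:

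| Test | 66 vs 198 | 74 vs 222 (no losses) |
|---|---|---|
| χ² with continuity correction | 65.2% | 71.5% |
| Fisher's exact | 69.8% | 75.3% |
| Pearson χ², uncorrected | 71.6% | 76.6% |
| Unpooled Wald test (matches the formula) | 78.3% | 82.4% |

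**5. True size at 66 versus 198**, with a common rate between 14% and 29%: about 5.0% for the uncorrected Pearson test and 2.8% to 3.4% for the corrected one. The correction therefore costs power without being needed to hold the 5% level.

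**6. What the sample can detect.** With ICC + MISA at 29% and 66 versus 198, exact power reaches 80% at a DCC + MISA rate of about 12.5% for the uncorrected test (81.3%; it is 79.8% at 12.75%). For the corrected test the rate is about 11.75% (80.7%; it is 79.1% at 12%).

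**7. What 80% at 14% would take.** The pooled formula gives 81 versus 243 evaluable infants without correction and 90 versus 270 with it. Exact power there is 80.4% and 80.9%. After 10% loss these become 90 versus 270 and 100 versus 300.

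**8. The ratio read literally.** With three DCC + MISA infants per ICC + MISA infant, the ICC + MISA count is 7.84 × (0.14 × 0.86/3 + 0.29 × 0.71)/0.0225 = 85.7, rounded up to 86, and the DCC + MISA count is 3 × 86 = 258. The stated 66 and 198 need the opposite order.

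**The case against.** The strongest reply is that nothing has been miscalculated. The formula is a standard one, is printed with its inputs, and gives exactly 66 and 198. For the unpooled test that matches it, exact power is 78.3%, close to target. That is true, but the analysis section does not name that test.

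The phrase allowing the test to be chosen as appropriate may reserve the correction and Fisher's test for sparse tables. The smallest expected count here is 66 × 0.2525, about 17, so the plain χ² could be what is meant. This is a fair reading. It moves the relevant figure from 65% to 72%, not to 80%.

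The 66 versus 198 comparison also assumes the full 10% is lost. Enrolment is 74 versus 222, the outcome falls at 36 weeks corrected age, and infants with incomplete information are excluded by criterion, so losses may be fewer. With none, the shortfall for the uncorrected test is about 3 points. It remains a shortfall, and an allowance meant for losses should not be counted as power.

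The inputs are themselves uncertain: the 29% comes from 31 infants and the 14% is an assumption. This limits how precisely any power figure should be read. It does not make the stated 80% right for the named test at the plan's own rates. An unadjusted logistic comparison does not rescue it either: at 66 versus 198 the exact power is 70.3% by Wald test and 74.2% by likelihood ratio.

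The reversed ratio is a wording slip whose intended direction is clear from the counts. It does not affect the design.

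**Conclusion.** The concern holds. At the plan's own rates and two-sided 5% level, no test named in the analysis section has the stated 80% power. With the planned losses, power is 65% to 72% and the chance of missing the assumed effect is 28% to 35%, not 20%. With no losses at all, power is 71% to 77%. The lower figure in each pair applies if the continuity correction is used, the upper if it is not; Fisher's exact test lies between. The cause is a mismatch between formula and test, not a slip in the plan's arithmetic.

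These figures concern the unadjusted two-group comparison of DCC + MISA with ICC + MISA at 29% and 14%. They do not describe a three-group test or a covariate-adjusted model. The order of the groups in the ratio sentence contradicts the counts in the same paragraph.

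**What to change.** 1. In Statistical analysis, name the uncorrected Pearson χ² for the 2×2 comparison of DCC + MISA with ICC + MISA on BPD, without continuity correction. An unadjusted logistic contrast is an acceptable alternative, but its power should then be quoted for the specific test (70% Wald, 74% likelihood ratio at 66 versus 198).
2. In Sample size calculation, restate power for 29% versus 14% as about 72% at 66 versus 198 and 77% at 74 versus 222. Alternatively, keep 80% and give the detectable DCC + MISA rate as about 12.5%.
3. Rewrite the ratio as 3:1 for ICC + MISA to DCC + MISA, and state the effect as a fall of 15 percentage points, from 29% to 14%.

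The cost is wording only, with a less favourable stated power and no extra infants. If the sponsor wants a true 80% at 14%, the uncorrected test needs 81 versus 243 evaluable infants, or 90 versus 270 after the 10% allowance. The prospective cohort is scheduled to run to October 2027, so the text can be corrected before the result is known.
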